#### General Issues

- Participation in other interventional drug trials

### 8.1.4 Females of childbearing age

Females can be included if they are unlikely to conceive, as indicated by at least one of the following points:

- Surgical sterilization
- Postmenopausal female > 45 years of age with > 2 years since last menses
- Non-sterilized, premenopausal, non-amenorrhoe female who agrees to abstain from heterosexual activity or to use an adequate method of contraception. Acceptable methods of

birth control are intrauterine device (IUD), diaphragm with spermicide, vasectomy, condom or hormonal contra-ceptives.

A pregnancy test will be performed at screening.

#### **8.1.5 Study duration**

The duration of treatment for each patient will be 7 days. On day 28 (+7) a follow-up and end of study interview will take place via telephone.

#### **8.1.6 Withdrawal and replacement of subjects**

##### **Criteria for withdrawal**

Subjects may prematurely discontinue from the study at any time. Premature discontinuation from the study is to be understood when the subject did not undergo End of Study (EOS) interview and / or all pivotal assessments during the study.

Subjects must be withdrawn under the following circumstances:

- at their own request
- if the investigator feels it would not be in the best interest of the subject to continue
- if the subject violates conditions laid out in the consent form / information sheet or disregards instructions by the study personal
- If the patient is in need of medication, which is not allowed according to 9.1.8
- allergies or idiosyncrasies to AP301 or any other inactive ingredient(s) of the investigational product

In all cases, the reason why subjects are withdrawn must be recorded in detail in the CRF and in the subject's medical records. Should the study be discontinued prematurely, all study materials (complete, partially completed and empty CRFs) will be retained.

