##### **Follow-up of patients withdrawn from the study**

In case of premature discontinuation after study drug intake, the investigations scheduled for the EOS visit will be performed on the day of study drug discontinuation. The subjects will be advised that participation in these investigations is voluntary. Furthermore, they may request that from the time point of withdrawal no more data will be recorded and that all biological samples collected in the course of the study will be destroyed.

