## Replacement policy

A sample size of 20 evaluable patients / group will be achieved. If applicable, drop-outs will be included in the sample size by using the Last Observation Carried Forward-method to complete the primary efficacy variable EVWL. If a patient cannot be included, he/she will be replaced by using the next free number of the respective stratum list.

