#### **9.5.4 End-of-study (EOS) interview (Day 28 + 7 days)**

On day 28 (+ 7) a follow-up/ EOS interview will take place via telephone. Survival will be documented. Adverse events and concomitant medication will be documented and the ventilation-free days (for > 48h) until day 28 will be listed. Furthermore, the duration of stay at ICU in the first 28 days and the duration of controlled ventilation period until extubation will be recorded.

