## **11. FOLLOW-UP**

### **11.1 Follow-up of study participants including follow-up of adverse events**

A follow-up/ end of study interview will be performed on day 28 (+7), about 21 days after end of treatment.

Follow-up of all SAEs will be done until the event is resolved or the event or sequel is stabilized.

Any medical-related issues or questions requiring immediate resolution or action should be directed to the Medical Supervisor.

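### Needing a prohibited medicine removes the patient from the study, so EVLW that could still be measured is left to LOCF and the Day 28 contact is set inconsistently

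*Protocol*

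**What the plan says.** Section 8.1.6 of the protocol opens by speaking of discontinuation from the study. It then introduces its criteria with "Subjects must be withdrawn under the following circumstances", and one of them reads "If the patient is in need of medication, which is not allowed according to 9.1.8". Section 9.1.8 names the medicines: steroids above 80 mg prednisolone or 300 mg hydrocortisone a day, cancer treatment, and transplant immunosuppression.

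Section 9.1.2 treats interrupting or stopping study drug as a separate matter, but 8.1.6 does not offer that as the response to this trigger. Section 9.1.3 closes the gap from the other side: when study drug is permanently stopped for a reason other than an adverse event, the patient is to leave the study, and the protocol labels this a withdrawal of consent.

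For patients who leave after taking study drug, the follow-up paragraph of 8.1.6 says that "the investigations scheduled for the EOS visit will be performed on the day of study drug discontinuation". It adds that participation is voluntary and that "they may request that from the time point of withdrawal no more data will be recorded". Section 9.5.5 asks for one further set of treatment-day or end-of-study investigations and gives no date.

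Missing EVLW is covered in 8.1.6 and again in 12.5: "If applicable, drop-outs will be included in the sample size by using the Last Observation Carried Forward-method".

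Three sections set the Day 28 contact with no exception for withdrawn patients: 8.1.5 ("On day 28 (+7) a follow-up and end of study interview will take place via telephone"), 9.5.4 ("On day 28 (+ 7) a follow-up/ EOS interview will take place via telephone") and 11.1 ("A follow-up/ end of study interview will be performed on day 28 (+7), about 21 days after end of treatment").

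**The concern.** The primary endpoint is the EVLW AUC from Day 0 to Day 7, and 12.1 keeps every randomised and dosed patient in the (modified) ITT set. A patient who starts high-dose steroids on Day 3 therefore belongs in that set, and EVLW can still be measured while the PiCCO system remains in place. The plan nevertheless ends the schedule for that patient and fills the remainder with a carried-forward value.

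The reason for the gap arises after randomisation and may be related to prognosis. LOCF then freezes the curve at the point where the clinical course may have changed. The direction of the error is not known in advance: it hides later improvement in some patients and later worsening in others.

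This is a rule of conduct, so an analysis plan written later can choose how to handle values but cannot recover those that were never taken. The protocol already takes the other course in a neighbouring case. When extubation ends dosing, 9.5.3 still has whatever continues to be measured documented.

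**Working it through.** **Reading the sections together**

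1. Is the withdrawal from the study? Yes. The opening of 8.1.6, the heading of its follow-up paragraph, and the non-adverse-event part of 9.1.3 all say so.
2. Is EVLW planned afterwards? At most once, if the undated set in 9.5.5 is read as a treatment-day assessment. No section schedules the 12-hourly series for these patients.
3. Is the Day 28 contact planned? Sections 8.1.5, 9.5.4 and 11.1 say yes for everyone. The follow-up paragraph of 8.1.6 moves the end-of-study investigations to the drug-stop day. The two do not agree.

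**The plan's own figure**

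Section 12.2 gives a difference of 40%, an SD of about 40%, 20 per group, two-sided 5% and 80% power. A two-sample t-test needs 16.7, so 17 per group. With 20 per group, power is 0.869. The stated size is sufficient.

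**How much of one patient's AUC is affected**

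Two values a day for 7 days give 14 values. After a trigger at the end of Day t, 14 − 2t are unplanned, a share of (7 − t)/7 of the period.

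If EVLW would have changed linearly by d (in % of baseline) over 7 days, LOCF misstates the 7-day mean by d(7 − t)²/98. A trapezoid on the 12-hour grid gives the same factors. The values of d are assumed.

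| Trigger, end of | Unplanned values | Share | Factor | d = 20% | d = 40% |
|---|---|---|---|---|---|
| Day 1 | 12 of 14 | 86% | 0.367 | 7.3 | 14.7 |
| Day 3 | 8 of 14 | 57% | 0.163 | 3.3 | 6.5 |
| Day 5 | 4 of 14 | 29% | 0.041 | 0.8 | 1.6 |

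**What that does to the comparison**

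The protocol gives no trigger rate, so the counts are assumed. All triggers are placed in the AP301 arm, the error is subtracted from the planned 40% difference, and the SD stays at 40%.

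- 2 of 20 at Day 3, d = 20% to 40%: (2/20) × 3.3 to 6.5 = 0.33 to 0.65 points. The difference becomes 39.67 to 39.35, with power 0.864 to 0.858.
- If the 40% difference in the 7-day mean comes from a flat placebo curve and a linear fall under AP301, d must be 80% at Day 7. Then:
  - 2 of 20 at Day 3: 38.69, power 0.846
  - 2 of 20 at Day 1: 37.06, power 0.815
  - 4 of 20 at Day 3: 37.39, power 0.821
  - 4 of 20 at Day 1: 34.12, power 0.748

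**Day 28**

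If status were not obtained for k of 20 patients in an arm, the best-to-worst range for that arm's survival widens by k/20: 5, 10 or 15 points for k = 1, 2 or 3. This is a bound and not an estimate of bias.

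**The case against.** The best case against the point is that it hardly matters. Patients already on these medicines are excluded at entry, so only new needs within the 7 treatment days affect the AUC. Power falls below 80% only when 4 of 20 patients in one arm trigger on Day 1 and the curves diverge by 80%. A patient at the entry minimum of 8 would then have to fall to 1.6, and nothing in the protocol supports that. The power figures also use a baseline SD for a 7-day AUC and leave it unchanged under LOCF, so the third decimal carries no meaning. All of this stands and limits the size of the point.

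A reader might infer that Day 28 survival, ICU stay and ventilator-free days are lost for these patients. The protocol does not say that. Three sections set the Day 28 contact without exception, 9.5.5 can be read as keeping it, and the opt-out from further recording makes sense only if recording can otherwise continue. Nor can Day 28 outcomes be collected on a Day 3 stop date. What stands is a contradiction to resolve, and those endpoints are descriptive under 12.6.2.

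Two practical objections also stand. Changing 8.1.6 alone would fail, because 9.1.3 would return the patient to study withdrawal. EVLW is also timed at 60 to 120 minutes after inhalation, so once dosing stops another time reference is needed.

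Finally, EVLW under high-dose steroids may not be what the primary analysis should use. That is a fair estimand question, but it can be settled either way only if the values exist.

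**Conclusion.** The point holds as a fault of conduct with a small expected effect. Sections 8.1.6 and 9.1.3 turn the need for a prohibited medicine into withdrawal from the study. The EVLW schedule then ends although measurement could continue, and the timing of the end-of-study contact is contradictory.

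For one affected patient, between 29% and 86% of the AUC period is left to LOCF, where it is applied, for triggers at Day 5 to Day 1. For the trial, 2 of 20 triggers at Day 3 leave power between 0.846 and 0.864, against 0.869 with none. This rests on assumed trigger counts, linear change, all triggers in one arm, and the baseline SD applied to the AUC.

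It would go too far to conclude that the primary comparison is seriously biased or underpowered: no trigger rate is given, and only an extreme combination takes power below 80%. The change is still worth making, because it is cheap and has to be made before the data are collected.

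**What to change.** - **8.1.6, criteria:** make the need for a 9.1.8 medicine a reason to stop study drug, not to leave the study. Record the medicine with date and dose.
- **9.1.3:** delete the rule that a permanent drug stop for a reason other than an adverse event means study withdrawal.
- **8.1.6, follow-up paragraph:** state that, unless the patient withdraws consent or asks that no more data be recorded, EVLW continues every 12 hours to Day 7 at the usual clock times while PiCCO is in place, and the end-of-study contact is made at Day 28.

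The cost is wording in two sections plus a clock-time rule to replace the post-inhalation window. The EVLW measurements and the telephone contact are already in the schedule. The downside is that some EVLW values will be taken under the prohibited medicine. Whether they enter the primary analysis is an estimand choice for the SAP, with a sensitivity analysis for the alternative.

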##### **Follow-up of patients withdrawn from the study**

In case of premature discontinuation after study drug intake, the investigations scheduled for the EOS visit will be performed on the day of study drug discontinuation. The subjects will be advised that participation in these investigations is voluntary. Furthermore, they may request that from the time point of withdrawal no more data will be recorded and that all biological samples collected in the course of the study will be destroyed.

## Replacement policy

A sample size of 20 evaluable patients / group will be achieved. If applicable, drop-outs will be included in the sample size by using the Last Observation Carried Forward-method to complete the primary efficacy variable EVWL. If a patient cannot be included, he/she will be replaced by using the next free number of the respective stratum list.

### 8.1.7 Premature termination of the study

The sponsor has the right to close this study at any time. The IEC and the competent regulatory authority must be informed within 15 days of early termination.

The trial will be terminated prematurely in the following cases:

- If adverse events occur which are so serious that the risk-benefit ratio is not acceptable.
- If the number of dropouts is so high that proper completion of the trial cannot realistically be expected.

## 9. METHODOLOGY

### 9.1 Study medication

#### Active agent and characteristics:

AP-301 is a TNF- $\alpha$ -derived alveolar epithelial sodium channel (ENaC) enhancing peptide that activates epithelial ion channels and facilitates fluid reabsorption in various animal models (in vitro, ex vivo, in situ and in vivo). In animal models AP 301 activates reabsorption of lung oedema of various pathophysiological origins, e.g. hydrostatic edema, the VALI- and ALI/ARDS-related permeability edemas, lung transplantation related edema, and edema caused by bacterial or viral pneumonias. The lectin-like domain of TNF- $\alpha$  also protects against the effects of free oxygen radicals and improves the epithelial cell function after tissue damage as seen in lung ischemia-reperfusion injury (LIRI).

The reference product will be a matching placebo formulation (0.9% NaCl solution (Ph.Eur.)).

The drug substance is the "Human Tumour Necrosis Factor alpha-derived peptide Cys-Gly-Gln-Arg-Glu-Thr-Pro-Glu-Gly-Ala-Glu-Ala-Lys-Pro-Trp-Tyr-Cys" and represents the "TIP-domain" of the Tumour Necrosis Factor alpha (TNF). The peptide is composed of 17 naturally occurring amino acids

and is circularised through an intramolecular disulfide bond between the N-terminal and C-terminal cysteine. It is soluble in water and has a molecular mass of 1,923.1. The drug substance AP301 peptide is produced by chemical peptide synthesis.

Manufacturer of Drug Product AP301 25 mg powder for reconstitution for solution for inhalation:  
Aptuit Glasgow, UK

#### Storage Instructions:

The drug product (Investigational Medicinal Product, IMP) "AP301 25 mg powder for reconstitution for solution for inhalation" is packed in Ph. Eur. Type I glass vials closed with a rubber stopper and sealed with a cap. It should be stored upright in a temperature monitored 2-8°C refrigerator until required. The refrigerator should be lockable.

The proposed shelf life at standard storage condition of 2-8°C is 15 months.

Route of administration:

Oral inhalation via nebulising device (Aeroneb® solo nebulisation system)

#### **9.1.1 Dosage and administration**

After patients meet inclusion criteria, in study group I orally delivered doses of 87.6 mg AP301 (dose per subject, 5 ml nebuliser filling dose) are inhaled every 12 hours ( $\pm$  30 min), for a total of 7 days. 87,6 mg AP301 are based on 125 mg nebuliser filling dose.

This dose level is well below the highest dose level used in the phase I study. It represents a dose level corresponding to the most effective dose levels used in pharmacologic studies.

After patients meet inclusion criteria, in study group II Placebo solution (0.9% physiologic NaCl, / 5 ml nebuliser filling dose) is inhaled every 12 hours ( $\pm$  30 min), for a total of 7 days.

To enable oral inhalation, reconstituted AP301 in WFI is converted into an inhalable aerosol by the Aeroneb Solo medicinal device. The Aeroneb Solo medicinal device is a product of Aerogen, Galway, Ireland and is a commercially available liquid nebuliser. The Aerogen Solo nebuliser has been approved in the European Community by CE-marking based on requirements of Annex II, Section 3.2. of Directive 93/42/EEC.

The nebulizer unit holds up to 6 ml of liquid medication. The nebulizer unit is clear to allow visual monitoring of medication levels and aerosolization. When the nebulizer unit is connected into the ventilator circuit, the silicon plug can be opened and closed in between doses without causing loss of circuit pressure.

### 9.1.2 Study drug interruption or discontinuation

The investigator must temporarily interrupt or permanently discontinue the study drug if continued administration of the study drug is believed to be contrary to the best interests of the patient.

The interruption or premature discontinuation of study drug might be triggered by an AE, a diagnostic or therapeutic procedure, an abnormal assessment (e.g., laboratory abnormalities), or for administrative reasons, in particular withdrawal of the patient's consent.

The reason for study drug interruption or premature permanent discontinuation must be documented in the CRF.

### 9.1.3 Study drug premature permanent discontinuation

#### **Study drug premature permanent discontinuation due to an adverse event**

If the reason for premature permanent discontinuation of study treatment is an AE, the patient should have a "Premature End of Study (EOS)" visit with all the assessments performed before the study drug discontinuation, whenever possible.

#### **Study drug premature permanent discontinuation due to another reason than adverse event**

If the reason for premature permanent discontinuation of study treatment is not an AE, the patient should be withdrawn from the study (withdrawal of consent) and have the end of study (EOS) visit with all the assessments performed before the study drug discontinuation, whenever possible.

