## **9.5 Study procedures**

### **9.5.1 General rules for trial procedures**

- All study measures like blood sampling and measurements (vital parameters, ECG, etc.) have to be documented with date (dd:mm:yyyy).
- There is a specific sequence for study procedures that should be followed: EVLW must be measured within 60 to 120 minutes after inhalation of IMP or placebo. All parameters should be assessed, if possible, as standardized as possible (e.g. daily between 08:00 a.m. and 10:00 a.m.).
- The dates of all procedures should be according to the protocol. The time margins mentioned in the study flow chart are admissible. If for any reason, a study procedure is not performed within scheduled margins a protocol deviation should be noted, and the procedure should be performed as soon as possible or as adequate.
- If a patient is extubated for more than 48 hours the patient will not receive any other study medication in case of re-intubation. Only if a patient is re-intubated within less than 48 hours administration of IMP or placebo will be continued until day 7.

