### 9.5.3 Treatment Phase (Day 1 to 7)

Randomization will be performed prior to first administration of study medication.

All of the following parameters will be measured once in 24 hours, EVLW values will be assessed every 12 hours (between 60 and 120 minutes after administration of IMP) until day 7.

Vital signs will be measured (pulse rate and respiratory rate). A blood sample for the evaluation of blood gases, clinical chemistry and hematology will be taken. The lung injury score (Murray, Matthay, Luce, & Flick, 1988) will be obtained. The EVLW will be measured via PiCCO® technique. Hemodynamic parameters will be analyzed. Adverse events and the concomitant medication will be recorded. Furthermore, the oxygenation index, the ventilatory plateau pressure and ventilation parameters will be obtained.

In case that a patient will be extubated during the treatment phase, no more study medication will be administered. If the patient is reintubated within 48 hours after extubation, study medication will be administered again (until day 7). Nonetheless, all parameters that still will be measured after extubation will be documented.

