### 12.6.2 Secondary endpoint analysis

Secondary efficacy variables are:

1. the treatment associated changes of oxygenation as measured by the  $\text{PaO}_2$  /  $\text{FiO}_2$  ratio until day 7 of therapy,
2. the ventilatory plateau pressure until day 7 of therapy,
3. the Murray lung injury score (a composite variable that includes components of oxygenation, compliance, positive end-expiratory pressure, and the appearance of the chest radiograph),
4. ventilation parameters: tidal volume ( $V_t$ ), positive endexpiratory pressure (PEEP), respiratory rate,  $\text{FiO}_2$ , PIP, mean airway pressure, peak airway pressure until day 7 of treatment
5. the duration of stay at ICU in the first 28 days,
6. the duration of controlled ventilation period until extubation,
7. the number of days free from ventilatory support [for > 48 h] in the first 28 days,
8. the survival status at day 28,
9. the local and systemic safety and tolerability and to identify possible dose related adverse events.

Secondary efficacy variables will be presented using appropriate descriptive methods, and will be analysed in an explorative sense: Mann-Whitney U-Test (Variable 1, 2, 3, 4), Kaplan-Meier estimates (variable 5, 6, 7, 8), and contingency tables (variable 9)

Statistical tests of the secondary efficacy variables and the p-values attached to them will be regarded as descriptive and not as tests of hypotheses.

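### Protocol 9.1.3 makes a non-AE stop of study drug a withdrawal from the study and, with 8.1.6, gives up later EVLW readings and true Day 28 outcomes

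*Protocol*

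**What the plan says.** Section 9.1.3 has two rules for permanent early discontinuation of study drug. After an adverse event (AE) the patient has a premature EOS visit. For every other reason it states: "discontinuation of study treatment is not an AE, the patient should be withdrawn from the study (withdrawal of consent"), again with an EOS visit.

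Section 9.1.2 shows how wide the other reasons are. Stopping "might be triggered by an AE, a diagnostic or therapeutic procedure, an abnormal assessment", or may be administrative; withdrawal of consent is one example among these.

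Section 8.1.6, on follow-up of withdrawn patients, states for early discontinuation after drug intake that "the investigations scheduled for the EOS visit will be performed on the day of study drug discontinuation". Its list of mandatory withdrawals includes a clinical need: "If the patient is in need of medication, which is not allowed according to 9.1.8".

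Extubation has its own text. Section 9.5.3: "In case that a patient will be extubated during the treatment phase, no more study medication will be administered", with resumption if the patient is re-intubated within 48 hours. Section 9.5.1: "If a patient is extubated for more than 48 hours the patient will not receive any other study medication in case of re-intubation". Section 9.5.3 then adds: "Nonetheless, all parameters that still will be measured after extubation will be documented".

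The efficacy list in 12.6.2 includes ICU stay and ventilator-free days in the first 28 days and "the survival status at day 28". Section 9.5.4 schedules their collection by telephone at Day 28 (+7 days).

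**The concern.** Stopping a treatment and leaving a trial are different events, and an intention-to-treat comparison depends on keeping them apart. Section 9.1.3 merges them for all non-AE stops and then labels the result withdrawal of consent. A patient whose drug is stopped for a procedure or an abnormal finding has not refused follow-up, yet is recorded as though consent had been withdrawn. Section 8.1.6 lets patients who withdraw ask that no more data be recorded, so the label also blurs who made that request and who did not.

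Two sets of data are at stake. The first is the remainder of the 12-hourly EVLW series that makes up the primary AUC from Day 0 to Day 7. The second is the set of 28-day outcomes, which cannot be known on the day the drug stops. The reasons for stopping are seldom unrelated to how the patient is doing, so the losses may depend on outcome and possibly on treatment arm. A later analysis plan cannot recover data that the protocol told the site not to collect.

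**Working it through.** The point rests on the text, so the rules are followed through for one patient. The only arithmetic is a count of readings.

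**Step 1: who falls under the rule.** The 9.1.3 heading covers any reason other than an AE. Combined with 9.1.2, it takes in procedures, abnormal assessments and administrative reasons as well as consent.

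**Step 2: what happens to that patient.** The patient leaves the study (9.1.3) and the EOS investigations take place on the day of the drug stop (8.1.6). The same-day timing comes from 8.1.6. Section 9.1.3 only asks for assessments before discontinuation where possible. Section 9.5.5 asks for the investigations of a treatment day or of the EOS interview, but gives no date and so does not restore Day 7 or Day 28 timing.

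**Step 3: what the analysis expects.** Section 12.1 defines the modified ITT set as randomized patients with at least one dose. Section 12.6.1 makes the full analysis population primary and uses it for all other efficacy variables; I take this to be the same set. The early stopper is therefore in the analysis, with ICU stay, ventilator-free days and survival due to Day 28.

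**Step 4: EVLW readings lost.** Input: one reading every 12 hours to Day 7 (Table 1 footnote; 9.5.3). Assuming two doses on each of 7 days, 2 × 7 = 14 post-dose readings are due. A patient who stops at the end of Day k has 2k of them and lacks 14 − 2k.

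| Stop at end of | Missing of 14 | Share |
|---|---|---|
| Day 1 | 12 | 86% |
| Day 2 | 10 | 71% |
| Day 3 | 8 | 57% |
| Day 4 | 6 | 43% |
| Day 5 | 4 | 29% |
| Day 6 | 2 | 14% |

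Sections 8.1.6 and 12.5 fill these gaps by LOCF. For a stop at the end of Day 3, more than half of the post-dose readings behind the AUC would repeat one earlier value.

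**Step 5: Day 28 outcomes.** Neither 8.1.6 nor 12.5 gives a rule for completing these. If the EOS assessment is made on Day 3, survival is known to Day 3, and ICU and ventilator-free days are known only up to then.

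**Step 6: AE stops.** These also get a premature EOS visit under 9.1.3, though without the statement that the patient is withdrawn. Whether they have a Day 28 contact is equally unclear.

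**Step 7: extubation.** It stops drug (9.5.3), permanently after more than 48 hours (9.5.1), and it is not an AE. No section says that it lies outside 9.1.3. Against that, 9.5.3 keeps documenting after extubation, and ventilator-free days to Day 28 presuppose that extubated patients are followed. The intent looks clear, but the text does not state it.

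**The case against.** The strongest defence is that the parenthesis in 9.1.3 limits the rule to real withdrawal of consent, which 9.1.2 also singles out. For a patient who refuses follow-up, nothing more could be collected anyway. This does not settle the matter. The heading and the sentence cover every non-AE reason, 9.1.2 names several that are not consent, and 8.1.6 separately requires withdrawal for a disallowed medicine.

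A reader might infer that the protocol orders recovering, extubated patients out of the study. The documents do not support that. Extubation is absent from the withdrawal criteria and from the discontinuation triggers, it has its own rules with continued documentation, and a stop that the protocol itself schedules need not be premature. What stands is an ambiguity that needs a sentence to close it. Equally, 9.5.3 covers only what is still measured, so it does not assure EVLW to Day 7 after extubation.

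A reader might also infer a fall in power by counting early stoppers as lost. The plan keeps drop-outs in the primary analysis through LOCF and gives no rate of non-AE stops, so no such figure follows.

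Nor does any section say that an early status will be reported as the Day 28 outcome. Section 12.6.2 uses Kaplan-Meier estimates for these variables and could censor early leavers, and it treats their tests as descriptive. That is fair and limits the consequence. Censoring at a drug stop that reflects the patient's condition may still be informative. That patients who need a disallowed medicine are deteriorating is plausible, but the document does not say so.

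**Conclusion.** The point holds as a defect of the text. Section 9.1.3 equates a non-AE drug stop with leaving the study and mislabels it as withdrawal of consent, and 8.1.6 brings the EOS investigations forward to the day of the stop. The firmest consequence is the loss of Day 28 survival, ICU-stay and ventilator-free-day data in patients who did not refuse follow-up. The second is a primary AUC completed by LOCF for anywhere from 2 to 12 of 14 post-dose readings per affected patient. That range assumes twice-daily dosing on all seven days and no EVLW reading after the stop.

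The number of patients affected is not given and cannot be derived. The harm is therefore potential bias, of unknown direction, together with missing 28-day data. It is not a quantifiable loss of power. The status of extubation under 9.1.3 is a gap to be reconciled, not an instruction to withdraw those patients.

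**What to change.** Reconcile 8.1.6, 9.1.3, 9.5.3 and 9.5.5 so that stopping study drug for any reason, extubation included, is not in itself withdrawal from the study. Keep withdrawal of consent as a separate category, recorded only when the patient actually withdraws it. Unless the patient withdraws consent to follow-up:

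- continue the scheduled EVLW readings to Day 7 for as long as the PiCCO catheter remains in place for care;
- collect survival, ICU days and ventilator-free days at Day 28, after AE and non-AE stops alike.

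Remove the rule in 8.1.6 that replaces the Day 28 EOS assessment with one on the day of drug discontinuation. An assessment at the stop can be kept in addition. The rules on when study drug is stopped or resumed stay as they are.

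The cost is amendment wording and a small extra data-collection effort. The Day 28 telephone call and the 12-hourly EVLW readings are already in the schedule.
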